### 4.9. Post hoc analyses

Any post-hoc, exploratory analyses which were not identified in this SAP but are completed to support the listed analyses will be identified clearly.

## 12. Descriptive analysis

A flow chart will be completed to describe participant flow from randomisation to 50 year follow-up.

Summary statistics will be presented for F1 participants included in the intention-to-treat analysis, with a comparison between characteristics of those followed up and those not followed up. Baseline demographic variables will be reported as mean and standard deviation or median and interquartile range where appropriate for continuous variables and as frequency and percentages for categorical variables.

### 13. Statistical Analysis

Statistical analysis will be performed for all primary, secondary and tertiary outcomes. Statistical significance will be tested at the 5% significance level using a two-sided test of significance. Analyses will compare the antenatal corticosteroid (betamethasone) group to the control (cortisone acetate) group.

Analyses for binary outcomes will be performed using log binomial regression analysis, reported as relative risk (RR) with 95% confidence intervals.

For continuous outcomes, analysis will be by general linear modelling after assessing model assumptions, using an identity link function and normal distribution.

For time-to-event analyses, a Cox proportional hazards model will be used, reported as a hazards ratio (HR) with 95% confidence intervals. The assumption of proportionality will be verified and if required time dependent functions modelled. Competing risk models will be used if appropriate.

For the hierarchical win-ratio outcome, analysis will follow a stepwise approach in which the six components of the composite outcomes are assessed sequentially (2). The six steps in the hierarchy will start with time to death after randomisation, followed by time to major adverse cardiovascular event, diagnosis of diabetes mellitus, number of admissions to hospital for respiratory illness, self-reported general health and time spent in hospital per 10 years alive. For each step, participants in the treatment and control group will be compared in all possible pairs to determine “wins”, “losses” and “ties”. Pairwise comparisons with ties or missing data at any step will be assessed at the next sequential step in the hierarchy. The analysis will then determine the ratio of the probability of wins and losses for the treatment. The resulting odds ratio will be reported with 95% confidence intervals (2).

## 14. Appendix

### 12.1 Flow diagram

[figure not shown]

[figure not shown]

## 12.2 Draft Tables

**Table 1 Baseline characteristics of those eligible who did and did not participate**

|                                                | Participated | Did not participate |
|------------------------------------------------|--------------|---------------------|
| Female (%)                                     |              |                     |
| Gestational age at entry, weeks (mean, SD)     |              |                     |
| Gestational age at delivery (mean, SD)         |              |                     |
| Multiple pregnancy (%)                         |              |                     |
| Singleton                                      |              |                     |
| Multiple                                       |              |                     |
| Unplanned premature labour (%)                 |              |                     |
| Planned delivery (%)                           |              |                     |
| Hypertension-oedema-proteinuria syndromes      |              |                     |
| Rh isoimmunisation                             |              |                     |
| Placenta praevia                               |              |                     |
| Diabetes mellitus                              |              |                     |
| Other                                          |              |                     |
| Mode of delivery (%)                           |              |                     |
| Normal vaginal delivery                        |              |                     |
| Instrumental delivery                          |              |                     |
| Caesarean section                              |              |                     |
| Tocolytic used (%)                             |              |                     |
| Ethanol                                        |              |                     |
| Salbutamol                                     |              |                     |
| Both                                           |              |                     |
| Treatment dose of betamethasone or placebo (%) |              |                     |
| Standard dose                                  |              |                     |
| Twice standard dose                            |              |                     |
| Term delivery (%)                              |              |                     |
| Birthweight, g (mean, SD)                      |              |                     |
| Birthweight Z score (mean, SD)                 |              |                     |
| 5 minute Apgar score <7 (%)                    |              |                     |

|                               |  |  |
|-------------------------------|--|--|
| Respiratory distress syndrome |  |  |
|-------------------------------|--|--|

**Table 2 Baseline characteristics of participants whose mothers were randomised to betamethasone and placebo**

|                                                | Betamethasone | Placebo |
|------------------------------------------------|----------------------|----------------|
| Maternal Characteristics                |                      |                |
| Gestational age at entry, days (mean, SD)      |                      |                |
| Gestational age at delivery, days (mean, SD)   |                      |                |
| Multiple pregnancy (%)                         |                      |                |
| Singleton                                      |                      |                |
| Multiple                                       |                      |                |
| Unplanned premature labour (%)                 |                      |                |
| Planned delivery (%)                           |                      |                |
| Hypertension-oedema-proteinuria syndromes      |                      |                |
| Rh isoimmunisation                             |                      |                |
| Placenta praevia                               |                      |                |
| Diabetes mellitus                              |                      |                |
| Other                                          |                      |                |
| Mode of delivery (%)                           |                      |                |
| Normal vaginal delivery                        |                      |                |
| Instrumental delivery                          |                      |                |
| Caesarean section                              |                      |                |
| Tocolytic used (%)                             |                      |                |
| Ethanol                                        |                      |                |
| Salbutamol                                     |                      |                |
| Both                                           |                      |                |
| Treatment dose of betamethasone or placebo (%) |                      |                |
| Standard dose                                  |                      |                |
| Twice standard dose                            |                      |                |
| Protocol deviations (%)                        |                      |                |
| Neonatal Characteristics                |                      |                |
| Female (%)                                     |                      |                |

|                                    |  |  |
|------------------------------------|--|--|
| Term delivery (%)                  |  |  |
| Birthweight, g (mean, SD)          |  |  |
| Birthweight Z score (mean, SD)     |  |  |
| 5 minute Apgar score <7 (%)        |  |  |
| Respiratory distress syndrome (%)  |  |  |
| Adult Characteristics       |  |  |
| Age at follow up, years (mean, SD) |  |  |
| Ethnicity (%)                      |  |  |
| Māori                              |  |  |
| New Zealand European               |  |  |
| Pacific                            |  |  |
| Other                              |  |  |
| Smoking status (%)                 |  |  |
| Non-smoker                         |  |  |
| Previously smoked                  |  |  |
| Currently smokes                   |  |  |

**Table 3 Primary outcomes**

|                                                                                          | Betamethasone
N = | Placebo
N = | Unadjusted
RR or HR
(95% CI) | Adjusted RR or
HR (95% CI) | P value |
|------------------------------------------------------------------------------------------|------------------------------|------------------------|---------------------------------------------|---------------------------------------|----------------|
| Cardiometabolic risk factor composite (%)                             |                              |                        |                                             |                                       |                |
| Time to first major adverse cardiovascular event
(median, 95% CI) |                              |                        |                                             |                                       |                |

Relative risk, Hazard ratio

**Table 4 Secondary outcomes**

| Outcome | Betamethasone
N = | Placebo
N = | Unadjusted
RR, HR, OR | Adjusted RR, HR
or mean | P value |
|----------------|------------------------------|------------------------|----------------------------------|------------------------------------|----------------|
|----------------|------------------------------|------------------------|----------------------------------|------------------------------------|----------------|

|                                                                                                                         |  |  | or mean
difference
(95% CI) | difference (95%
CI) |  |
|-------------------------------------------------------------------------------------------------------------------------|--|--|-----------------------------------|------------------------|--|
| Diabetes mellitus or prediabetes (n/N, %)                                                                   |  |  |                                   |                        |  |
| Diabetes mellitus (n/N, %)                                                                                  |  |  |                                   |                        |  |
| Prediabetes (n/N, %)                                                                                        |  |  |                                   |                        |  |
| Hypertension (n/N, %)                                                                                       |  |  |                                   |                        |  |
| Dyslipidaemia (n/N, %)                                                                                      |  |  |                                   |                        |  |
| Age at cardiovascular death (median, 95% CI)                                                                |  |  |                                   |                        |  |
| Proportion with cardiovascular death (n/N, %)                                                               |  |  |                                   |                        |  |
| Age at first admission for myocardial infarction or
coronary revascularisation (median, 95% CI)          |  |  |                                   |                        |  |
| Age at first admission for myocardial infarction
(median, 95% CI)                                        |  |  |                                   |                        |  |
| Age at first admission for coronary revascularisation
(median, 95% CI)                                   |  |  |                                   |                        |  |
| Age at first admission for peripheral vascular disease
(median, 95% CI)                                  |  |  |                                   |                        |  |
| Age at first admission for arterial thrombosis/embolism
(median, 95% CI)                                 |  |  |                                   |                        |  |
| Age at first admission for peripheral revascularisation
procedure (median, 95% CI)                       |  |  |                                   |                        |  |
| Age at first admission for stroke (median, 95% CI)                                                          |  |  |                                   |                        |  |
| Age at first heart failure admission (median, 95% CI)                                                       |  |  |                                   |                        |  |
| Proportion with at least one admission for myocardial
infarction or coronary revascularisation (n/N, %)  |  |  |                                   |                        |  |
| Proportion with at least one admission for myocardial
infarction (n/N, %)                                |  |  |                                   |                        |  |
| Proportion with at least one admission for coronary
revascularisation (n/N, %)                           |  |  |                                   |                        |  |

|                                                                                                                                                           |  |  |  |  |  |
|-----------------------------------------------------------------------------------------------------------------------------------------------------------|--|--|--|--|--|
| Proportion with at least one admission for peripheral vascular disease (arterial thrombosis/embolism or need for revascularisation) (n/N, %)  |  |  |  |  |  |
| Proportion with at least one admission for arterial thrombosis/embolism (n/N, %)                                                              |  |  |  |  |  |
| Proportion with at least one admission for peripheral revascularisation procedure (n/N, %)                                                    |  |  |  |  |  |
| Proportion with at least one admission for stroke (n/N, %)                                                                                    |  |  |  |  |  |
| Proportion with at least one admission for heart failure (n/N, %)                                                                             |  |  |  |  |  |
| Win-odds Hierarchical outcome                                                                                                                 |  |  |  |  |  |
| Time to death after randomisation (median, 95% CI)                                                                                            |  |  |  |  |  |
| Time to MACE (excluding cardiovascular death) (median, 95% CI)                                                                                |  |  |  |  |  |
| Diagnosis of diabetes mellitus (excluding prediabetes) (n/N, %)                                                                               |  |  |  |  |  |
| Number of admissions to hospital with respiratory illness as primary reason for admission (admissions per patient year) (mean, SD)            |  |  |  |  |  |
| Self-reported general health (mean, SD)                                                                                                       |  |  |  |  |  |
| Time in Hospital per 10 years alive after 1988 (median, 95% CI)                                                                               |  |  |  |  |  |
| Ischaemic heart disease (n/N, %)                                                                                                              |  |  |  |  |  |
| Stroke (n/N, %)                                                                                                                               |  |  |  |  |  |
| Peripheral vascular disease (n/N, %)                                                                                                          |  |  |  |  |  |
| Overweight or obesity (n/N, %)                                                                                                                |  |  |  |  |  |
| BMI (continuous) (mean, SD)                                                                                                                   |  |  |  |  |  |
| Death from any cause (n/N, %)                                                                                                                 |  |  |  |  |  |
| Time to death after randomisation (mean, SD)                                                                                                  |  |  |  |  |  |
| Time in Hospital per 10 years alive after 1988 (mean, SD)                                                                                     |  |  |  |  |  |

|                                                                                                                                                                                                                                            |  |  |  |  |  |
|--------------------------------------------------------------------------------------------------------------------------------------------------------------------------------------------------------------------------------------------|--|--|--|--|--|
| Self-reported general health (mean, SD)                                                                                                                                                                                        |  |  |  |  |  |
| Rate of admissions to hospital with respiratory illness as the primary reason for admission/per patient year of followup (mean, SD)                                                                                            |  |  |  |  |  |
| Chronic respiratory illness (Self-reported diagnosis of asthma, self-reported chronic respiratory symptoms, admissions for asthma or chronic obstructive pulmonary disease [COPD] or prescription of pharmaceuticals for asthma or COPD) c |  |  |  |  |  |
| Asthma (n/N, %)                                                                                                                                                                                                                |  |  |  |  |  |
| Chronic respiratory symptoms (n/N, %)                                                                                                                                                                                          |  |  |  |  |  |
| Proportion with at least one admission for asthma or chronic obstructive pulmonary disease (COPD) (n/N, %)                                                                                                                     |  |  |  |  |  |
| Prescriptions of pharmaceuticals for asthma or COPD (n/N, %)                                                                                                                                                                   |  |  |  |  |  |
| Highest level of educational attainment (n/N, %) 
Tertiary
Secondary
Neither tertiary nor secondary                                                                                                                   |  |  |  |  |  |

Relative risk, Hazard ratio, Mean difference, Hierarchical win ratio outcome: 6 step, unmatched, win ratio hierarchy including time to death after randomisation; time to first major adverse cardiovascular event (MACE); diagnosis of diabetes mellitus; number of admissions to hospital with respiratory illness as primary reason for admission; self-reported general health; time in hospital per 10 years alive after 1988

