**Reproductive system outcomes: Female**

- Age at menarchecS
- Number who have reached menopause and age at menopausecS
- Need for assisted reproductive technologycS
- Polycystic ovarian syndromecS
- Total number of pregnancies  $\geq 20$  weeks (parity)cS

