| Age at menopause (mean, SD)                                                                                                         |  |  |  |  |  |
| Need for assisted reproductive technology (n/N, %)                                                                                  |  |  |  |  |  |
| Polycystic ovarian syndrome (n/N, %)                                                                                                |  |  |  |  |  |
| Total number of pregnancies ≥20 weeks (parity)
(median, 95% CI)                                                                  |  |  |  |  |  |
| Diagnosis or treatment of a mental health disorder
(n/N, %)                                                                      |  |  |  |  |  |
| Depression (n/N, %)                                                                                                                 |  |  |  |  |  |
| Bipolar affective disorder (n/N, %)                                                                                                 |  |  |  |  |  |
| Anxiety disorder (n/N, %)                                                                                                           |  |  |  |  |  |
| Schizophrenia (n/N, %)                                                                                                              |  |  |  |  |  |
| Inpatient admission for a mental health disorder
(excluding mental disorders due to known physiological
conditions) (n/N, %)  |  |  |  |  |  |
| Prescriptions of pharmaceuticals for mental health
disorders (n/N, %)                                                            |  |  |  |  |  |
| Total number of fractures (median, 95% CI)                                                                                          |  |  |  |  |  |
| Cancer diagnosis (n/N, %)                                                                                                           |  |  |  |  |  |
| Allergic condition other than asthma (diagnosis of or
prescription of treatments for allergic conditions) (n/N,
%)            |  |  |  |  |  |
| Chronic kidney disease (n/N, %)                                                                                                     |  |  |  |  |  |

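### Tables 4 and 5 assign a mean difference to time to death and to age at menopause, both right-censored at about 50 years, with no rule for participants without the event

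*SAP*

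**What the plan says.** **Time to death.** Table 4 of the SAP shows it twice. One row, "Time to death after randomisation (median, 95% CI" and so on, is a component of the win ratio and carries footnote 4. A later row, "Time to death after randomisation (mean, SD" and so on, carries footnote 3, defined under the table as "3 Mean difference". Section 5.2 gives time to death denominator a, all participants whose mothers were randomised.

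**Age at menopause.** Section 5.3 lists the outcome as "Number who have reached menopause and age at menopause". Table 5 splits it into a proportion with a relative risk and a row "Age at menopause (mean, SD" and so on, again with footnote 3.

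**Methods.** Section 13 states: "For time-to-event analyses, a Cox proportional hazards model will be used", with a hazard ratio, a check of proportionality and time-dependent functions if required. It also states: "For continuous outcomes, analysis will be by general linear modelling after assessing model assumptions". A row marked as a mean difference therefore calls on the linear model. In Table 4 the sibling row for age at cardiovascular death carries footnote 2, the hazard ratio.

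**Missing values.** The section on withdrawals, missing data and outliers plans no imputation. No passage says what value a survivor, or a woman who has not reached menopause, takes in a mean.

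**The concern.** A person alive at follow-up has no time to death, and a woman still menstruating has no age at menopause. Each has only a lower bound. A linear model of a mean difference cannot use a lower bound, so someone must decide at the analysis stage who enters the mean and with what value. The easiest choice is to use only those with an observed event, and that selects on the outcome.

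The direction matters most for time to death. Deaths in this cohort fall into an early group around birth and a late adult group. Extra adult deaths raise the average age of those who died. In a study that looks for late harm, a measure that can show more late deaths as a longer time to death is a poor choice.

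**Working it through.** The plan gives no figure for either row, so there is nothing to reproduce. The inputs below are assumptions, used to show direction and size.

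**1. Time to death, main example.** Assume 10% neonatal deaths (time about 0) in both arms, and later deaths at a mean age of 35 years in 8% of the steroid arm and 5% of the control arm.

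- Mean among decedents = (late share × 35) / (all deaths). Steroid: 0.08 × 35 / 0.18 = 15.6 years. Control: 0.05 × 35 / 0.15 = 11.7 years. Difference: **+3.9 years**, an apparent benefit.
- Restricted mean to 50 years over all offspring = late share × 35 + surviving share × 50. Steroid: 0.08 × 35 + 0.82 × 50 = 43.80. Control: 0.05 × 35 + 0.85 × 50 = 44.25. Difference: **-0.45 year**, the true harm.

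**2. Time to death, other inputs.** Early deaths at 0.02 year and late deaths at 40 years, per 100 offspring:

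| Control (early + late) | Steroid (early + late) | Decedents' mean, control v steroid (years) | Difference | Restricted mean difference to 50 years |
|---|---|---|---|---|
| 15 + 5 | 15 + 10 | 10.0 v 16.0 | +6.0 | -0.5 |
| 10 + 5 | 10 + 8 | 13.3 v 17.8 | +4.4 | -0.3 |
| 15 + 5 | 10 + 5 | 10.0 v 13.3 | +3.3 | +2.5 |
| 15 + 5 | 10 + 10 | 10.0 v 20.0 | +10.0 | +2.0 |

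The sign reverses in the two rows with equal early deaths. Where early deaths fall, as the study hypothesis expects, the sign agrees but the size does not. In the last row a doubling of late deaths raises the decedents' difference from +3.3 to +10.0, while the restricted mean difference falls from +2.5 to +2.0.

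**3. Age at menopause.** Assume normal ages with means 51 v 50 and SD 4, seen only if menopause came before assessment age A. The mean among women already menopausal is μ − σφ(b)/Φ(b), with b = (A − μ)/σ.

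| A | Observed means (years) | Observed difference (true 1.0) | Not yet menopausal |
|---|---|---|---|
| 48 | 45.68 v 45.44 | 0.25 | 77% v 69% |
| 50 | 47.15 v 46.81 | 0.34 | 60% v 50% |
| 52 | 48.42 v 47.96 | 0.45 | 40% v 31% |

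The difference keeps its sign but loses more than half its size.

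**4. Medians in the arm columns.** Table 3 asks for a median with 95% CI for "Time to first major adverse cardiovascular event", and Table 4 does so for the age-at-first-event rows. Section 9 assumes 8% with an event in each group, so about 92% remain event-free. The curve does not fall to 50%, and no median exists. Events that are components of the composite cannot be more frequent than the composite itself.

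**The case against.** The strongest reply is that the plan nowhere asks for a mean among deaths only. A reader might infer it from the table row, but denominator a points the other way: it includes survivors, and a mean over everyone with survivors counted at 50 years gives 43.80 v 44.25 and the right sign. This stands. The sign reversal is therefore a risk of an unstated rule, not a stated method. What remains is that the rule for survivors is missing and the row conflicts with section 13.

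Mortality is also not hidden. The row just above reports death from any cause with a relative risk, and time to death leads the win ratio hierarchy. In the main example the reader would see 18% v 15% next to the odd mean. This limits the harm but does not make the mean difference valid.

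Three further readings are tempting and not supported:

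- That a primary effect measure is biased. The major cardiovascular event outcome and the age-at-first-admission rows keep a hazard ratio. Only their arm medians will not be reached.
- That most women are censored. The SAP does not say so. Under the inputs above the share runs from 31% to 77% with assessment age.
- That the menopause row contradicts section 13. That section does not class it as time-to-event. The fault there is the missing rule for censoring, partly disclosed by the paired proportion.

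Lastly, one hazard ratio can itself mask opposite trends. With 10 early + 8 late deaths v 15 + 5 per 100, treating hazards as proportional, it is ln(0.82)/ln(0.80) = 0.89 despite more late deaths. That is fair, and the fix must allow for it.

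**Conclusion.** The point holds for two rows, one secondary and one tertiary, in tables headed as drafts. As written, each assigns an effect measure that does not fit a right-censored outcome, and the time-to-death row also departs from section 13 and from its sibling row for age at cardiovascular death. The impact is moderate. If the mean is taken among those with the event, the time-to-death difference can reverse sign (+3.9 against -0.45 year in the main example; +6.0 against -0.5 and +4.4 against -0.3 in others), and a 1.0-year menopause difference shrinks to 0.25 to 0.45 year. These sizes rest on assumed death rates, ages at death and menopause distributions, none of which the SAP gives. The reversal was found with equal early deaths in the two arms. The unreached medians are a matter of presentation only.

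**What to change.** - **Table 4, time to death.** Replace the mean-difference row by a Cox hazard ratio (footnote 2) in all offspring of randomised mothers, censored at the date last known alive. Apply the proportionality check and time-dependent modelling of section 13, because early and late deaths may move in opposite directions. A restricted mean survival difference to 50 years is an acceptable addition. The existing relative-risk row for any death stays.
- **Table 5, age at menopause.** Use a censored time-to-event method, with women not yet menopausal censored at their age at the questionnaire. Name the outcome under the time-to-event paragraph of section 13, and keep the proportion row.
- **Tables 3 and 4, arm summaries (presentation only).** For the age-at-first-event rows, show number of events and cumulative incidence at age 50 with 95% CI in place of the median.

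The cost is edits to table shells and footnotes and a few lines in section 13. The Cox method is already planned. The menopause analysis needs each woman's age at the questionnaire, and the time-to-death analysis needs a date last known alive.
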